## Abstract

**Background:**

The early diagnosis of atherosclerotic disease is essential for developing preventive strategies in populations at high risk and acting when the disease is still asymptomatic. A low ankle-arm index (AAI) is a good marker of vascular events and may be diminished without presenting symptomatology (silent peripheral arterial disease). The aim of the PERART study (PERipheral ARTerial disease) is to determine the prevalence of peripheral arterial disease (both silent and symptomatic) in a general population of both sexes and determine its predictive value related to morbimortality (cohort study).

**Methods/Design:**

This cross-over, cohort study consists of 2 phases: firstly a descriptive, transversal cross-over study to determine the prevalence of peripheral arterial disease, and secondly, a cohort study to evaluate the predictive value of AAI in relation to cardiovascular morbimortality.

From September 2006 to June 2007, a total of 3,010 patients over the age of 50 years will be randomly selected from a population adscribed to 24 healthcare centres in the province of Barcelona (Spain).

The diagnostic criteria of peripheral arterial disease will be considered as an AAI < 0.90, determined by portable Doppler (8 Mhz probe) measured twice by trained personnel. Cardiovascular risk will be calculated with the Framingham-Wilson tables, with Framingham calibrated by the REGICOR and SCORE groups. The subjects included will be evaluted every 6 months by telephone interview and the clnical history and death registries will be reviewed. The appearance of the following cardiovascular events will be considered as variables of response: transitory ischaemic accident, ictus, angina, myocardial infartction, symptomatic abdominal aneurysm and vascular mortality.

**Discussion:**

In this study we hope to determine the prevalence of peripheral arterial disease, especially the silent forms, in the general population and establish its relationship with cardiovascular morbimortality. A low AAI may be a better marker of arterial disease than the classical cardiovascular risk factors and may, therefore, contribute to improving the predictive value of the equations of cardiovascular risk and thereby allowing optimisation of multifactorial treatment of atherosclerotic disease.

## Background

Prevention and early diagnosis of atheroslerotic disease is one of the essential objectives of the field of cardiovascular disease since it is the main cause of mortality in developed countries. In Spain, cardiovascular diseases are the first cause of death, producing 34% of all deaths [1], with ischaemic heart disease causing the greatest number of cardiovascular deaths (31%) followed by cerebrovascular disease (29%) [1].

Atherosclerosis is currently considered a chronic, progressive, systemic disease, the genesis of which involves complicated pathogenic mechanisms. This disease is characterised by remaining clinically silent during most of its evolutive process until the sudden appearance of complications of the atherosclerotic plaques which lead to ischaemic vascular events. From primary prevention point of view, it is therefore very important to develop strategies to identify patients with subclinical stages of arteriosclerosis.

Atherosclerotic disease is characterised by a multifactorial aetiology constituted by different risk factors which potentiate among themselves and which are often presented in asssociation [2]. Risk factors which may be modified include arterial hypertension, hypercholesterolemia, diabetes mellitus, and smoking, while age and sex are non modifiable factors. Other risk factors act through intermediate risk factors such as abdominal obesity [3,4], sedentarism, or a family history of early coronary heart disease. These risk factors have been integrated in prediction tables based on regression models with the aim of detecting the population at high risk of presenting cardiovascular events [5]. However, the sensitivity and positive predictive value of these tables is low and, thus, most cardiovascular diseases are produced in persons without a high risk [5]. It is, therefore, important to develop markers of silent ateriosclerotic disease which may aid to better define the patients at high risk and to thereby act early and intensively to prevent the appearance of cardiovascular diseases with pharmacologic and non pharmacologic measures.

The ankle-arm index (AAI) is the result of the quotient obtained by dividing systolic arterial pressure (SAP) at the level of the posterior pedial or tibial artery between the brachial SAP by Doppler [6]. Low values of AAI determination (<0.9) allow the diagnosis of peripheral arterial disease (PAD) in asymptomatic patients [7]. An AAI of < 0.9 has a sensitivity of 95% and a specificity of 99% for angiographically demonstrated PAD [8]. Determination of the AAI also allows the quantification of the severity of PAD: mild (AAI = 0.7 – 0.9), moderate (AAI = 0.5 – 0.69) and severe stenosis (AAI = <0.5).

In some studies a low AAI has shown to be a good marker of vascular events [8]. In the Atherosclerosis Risk in Communities (ARIC) Study [9,10], the AAI was inversely associated with coronary disease, ictus and atherosclerosis at the level of the carotid and popliteal arteries. The Edinburgh Artery Study [11] reported a relative risk of ictus of 1.98 (CI 95%; 1.05 – 3.77) in patients with an AAI < 0.9. In a Swedish cohort of males over the age of 68 years [12] followed over 10 years, the relative risk of ischaemic ictus for an AAI = 0.9 was 2.0 (95% CI; 1.1 – 3.7). These results, however, do not agree in all studies. In the Cardiovascular Health Study [7], an assocation was found between a low AAI and the risk of vascular events in general, but no relationship was observed between an AAI < 0.9 and the risk of ictus. In addition, in the Pittsburgh study the risk of cardiovasscular events significantly increased only above an AAI < 0.7 [13].

Another aspect requiring clarification is the prognostic value of AAI in a medium with a low prevalence of cardiovascular diseases such as in Spain and other Mediterranean countries [14].

Moreover, the PAD is a significant predictor of cardiovascular mortality [15-17]. Mortality is also greater in patients with asymptomatic PAD compared to patients without arterial disease [16,18,19]. Some studies [7] have suggested that PAD in females represents a greater cardiovascular morbidity while in males this disease represents a higher mortality rate.

The prevalence of PAD ranges between 1.8% and 25% according to the population, the medium studied and the cut-off value of the AAI [11,20-25]. Likewise, the prevalence is higher in determined populational subgroups such as diabetics [20] and smokers [23]. No populational based studies are available in Spain, with the studies found being carried out in selected populations [26-34].

The present study will have two phases. The main objective of the first phase (cross-over study) is to determine the prevalence of PAD in the general population, in both its silent and symptomatic forms. The secondary objective is to study the association of PAD, especially in the silent forms, with other prevalent cardiovascular events and cardiovascular risk factors. The main objective of the second phase (cohort study) is to determine the incidence of cardiovascular events in patients with PAD and quantify the risk of having these events. The secondary objective in this phase is to study the predictive value of AAI with respect to the risk of having cardiovascular events in relation to the equations of cardiovascular risk (Framingham-Wilson, Framingham calibrated by REGICOR and SCORE).

## Methods/Design

This is a two-phase study. The first phase is a transversal, multicentre, descriptive study the aim of which is to determine the prevalence of symptomatic and asymptomatic PAD in a general population attended in primary care. The secondary aim is to study the association of PAD, especially in the silient forms, with other previous or prevalent cardiovascular events and cardiovascular risk factors. The second phase is a cohort study, the main objectives of which are to determine the incidence of cardiovascular events in patients with and without PAD and to quantify the risk of having these events. The secondary objective is to study the predictive value of AAI with respect to the risk of having cardiovascular events in relation to the equations of cardiovascular risk (Framingham, Framinham calibrated by REGICOR and SCORE). An initial 5-year follow up will be carried out in the cohorts generated in phase I: subjects without PAD and subjects with PAD and the cardiovascular morbimortality will be analysed. This study has been approved by the local Ethics Committee (Jordi Gol i Gurina Foundation of Investigation in Primary Care). Informed written consent will be obtained from all the participants. Likewise, the recommendations of the World Medical Assocation Declaration of Helsinki will be followed [35].

### Setting

This study will be performed in a total of 24 healthcare centres within the metropolitan area of the city of Barcelona and the county of North Barcelona – Maresme, including urban and semi-rural healthcare centres. These centres cover a population of approximately 600,000 inhabitants.

### Study Population and subjects

A simple randomised sample will be undertaken until achieving the required sample size. Figure 1 provides a flow diagram of the study.

**Figure 1 F1:**
[figure not shown]
Flow diagram of the study.

### Data collection

Data will be collected in a questionnaire specifically designed for this study. Prior to initiation of the study a pilot trial will be performed in 120 cases to detect errors in its design, to test the questionnaire interviewers and to verify concordance in data collection (data validation).

#### Baseline data collections (cross-over study)

The following variables will be studied.

-Demographic, cultural and economic variables related to the capacity of physical strength, with a previously validated questionnaire [36], related to menopause, family history of early cardiovascular death, personal history of cardiovascular disease, acute myocardial infarction, angina, cerebrovascular accident [14]. Similarly, the clinical history will be verified if the patient is diagnosed with ictus (CIE 10 code: I64), transitory ischaemic accidents (CIE 10 code: G45), angina (CIE 10 code: I20.0), acute myocardial infarction (CIE 10 code: I25) and PAD of the lower extremities (CIE 10 code: I73.9). Personal history of hypercholesterolemia, diabetes mellitus, arterial hypertension and smoking, establishing the history and current status of the smoking habit in the latter case [14,37-39].

-Anthropometric variables, current systolic/diastolic blood pressure values, blood analysis (total cholesterol, HDL-cholesterol, DLD-cholesterol, triglycerides and glycaemia [glycosylated haemoglobin (HbA1c) in diabetics], except in the case of having a recent analysis within the last 12 months, and standard electrocardiogramme [40]. Calculation of cardiovascular risk with the Framingham-Wilson equations [40], Framingham calibrated by the REGICOR [41] and SCORE [42] groups, and medications taken considering current drug intake (at least 1 tablet/day) of the following pharmacological groups: lipid-lowering drugs, antiaggregants, anticoagulants, antihypertensives and hypoglycidemiants [43,44]; Edinburgh vascular questionnaire [45].

The ankle-arm index (AAI) examination of the subjects will be carried out in the 24 healthcare centres participating in the study by two healthcare professionals trained in the technique. The AAI will be performed in the two paramaleolar arteries of both lower extremities, taking into consideration the lowest of four AAI determinations. If the result is < 0.9, the technique will be performed by the other professional. In cases in which the second professional finds an AAI>= 0.9, the first will repeat the test and the latter value will be considered as the final result. AAI measurement will be performed by the standardised procedure [6].

Patients with peripheral arterial disease will be referred to the general practitioner of the healthcare centre to which the patient is adscribed to follow the protocols of the centre. If the AAI is lower than 0.5, the patient will be referred to the vascular surgeon of reference.

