#### Morbidity

-Coronary disease: 1) angina, 2) acute myocardial infarction

-Cerebrovascular disease: 1) transient ischaemic attack, 2) ictus

-Symptomatic aneurysm of the abdominal aorta

These events will be confirmed by a cardiologist, neurologist and vascular surgeon, respectively.

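### Three of the five ICD-10 codes used to verify previous cardiovascular events do not match the disease named beside them (I25 for acute infarction, I20.0 for angina, I64 for stroke)

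*Protocol article*

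**What the plan says.** The protocol article, under Baseline data collections (cross-over study), gathers previous disease in two ways. The questionnaire asks about "personal history of cardiovascular disease, acute myocardial infarction, angina, cerebrovascular accident [14". The record is then checked against codes:

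- stroke: "the clinical history will be verified if the patient is diagnosed with ictus (CIE 10 code: I64"
- transient ischaemic attack: "transitory ischaemic accidents (CIE 10 code: G45"
- angina and infarction: "angina (CIE 10 code: I20.0), acute myocardial infarction (CIE 10 code: I25"
- peripheral arterial disease: "PAD of the lower extremities (CIE 10 code: I73.9"

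The article does not say whether a diagnosis filed under another code counts. It also does not say which source prevails if questionnaire and record disagree.

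These previous events feed the secondary objective of phase 1, stated under Methods/Design as the association of PAD "with other previous or prevalent cardiovascular events and cardiovascular risk factors". Follow-up events in phase 2 are handled differently. The Morbidity section gives no codes for them and states: "These events will be confirmed by a cardiologist, neurologist and vascular surgeon, respectively".

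**The concern.** The article names a coding system and prints one code against each disease, so a centre would reasonably take the printed code as the thing to look for. Three of the five codes do not describe the disease beside them. A record reviewer who follows the list literally would:

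- not verify an infarction filed under I21 or I22;
- accept as infarction a patient with chronic ischaemic heart disease who never had one;
- pass over stable angina;
- pass over a stroke that had been typed as ischaemic or haemorrhagic.

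At stake are the recorded frequencies of previous infarction, angina and stroke, their associations with PAD in phase 1, and any baseline cardiovascular-disease term among the covariates of the Cox models, which the article leaves open. With 24 centres and no rule for conflicting sources, centres could also resolve the same conflict differently.

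**Working it through.** **Step 1. Codes against labels.** The article prints the codes but not their meanings. The meanings below are the standard headings of the classification that it names.

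| Disease named | Code printed | ICD-10 heading | Fit |
|---|---|---|---|
| Stroke | I64 | Stroke not specified as haemorrhage or infarction | Too narrow: omits specified strokes (I60-I63) and sequelae (I69) |
| Transient ischaemic attack | G45 | Fits label | Keep |
| Angina | I20.0 | Unstable angina | Too narrow: omits I20.1-I20.9 |
| Acute myocardial infarction | I25 | Chronic ischaemic heart disease | Omits I21-I22; includes old infarction (I25.2) and also disease without infarction |
| PAD of the legs | I73.9 | Fits label | Keep |

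For angina the problem shows partly in the form of the code. I20.0 is one subcode of I20, yet it stands against the unrestricted word angina, which the Morbidity section also uses without restriction.

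**Step 2. What under-recording does (stroke, angina).** Let p1 and p0 be the true prevalences of a previous event with and without PAD, and s the share of true cases that the code picks up. If s is the same in both groups and there are no false positives, the recorded prevalences are s·p1 and s·p0.

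- Prevalence ratio: (s·p1)/(s·p0) = p1/p0, unchanged.
- Illustration with assumed values p1 = 8%, p0 = 4%, s = 50%: the ratio is 8/4 = 2.0 before and 4/2 = 2.0 after. The odds ratio is (0.08/0.92)/(0.04/0.96) = 2.09 before and (0.04/0.96)/(0.02/0.98) = 2.04 after.
- Prevalence and precision do suffer. If 30% to 70% of past strokes carry a specific code (assumed; no figure in the documents), then s runs from 70% down to 30%. For an uncommon event, the standard error of the log ratio grows by about 1/√s: 1/√0.7 = 1.20 to 1/√0.3 = 1.83.

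**Step 3. What a mixed category does (infarction).** Let f1 and f0 be the shares of each group who carry an I25 code but never had an infarction. The recorded prevalences are s·p1 + f1 and s·p0 + f0, and their ratio is (s·p1 + f1)/(s·p0 + f0). It equals p1/p0 only if f1/f0 = p1/p0. Otherwise the association reported for infarction is a blend of infarction and chronic ischaemic disease without infarction. The documents give none of s, f1 or f0, so neither size nor direction can be computed.

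**Step 4. Where these variables go.** Previous events enter the phase 1 secondary objective and possibly the Cox covariates. PAD itself is defined by an ankle-arm index below 0.9, and the Follow up section forms the two cohorts on that index alone. Neither depends on the codes.

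**The case against.** **The code meanings are not in the article.** This is true. But the article adopts a named public classification and prints codes from it, so reading those codes by their headings is reading the protocol's own terms. How these centres actually file events is not known, and that limits any statement about size.

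**The codes are not declared to be the case definition.** This stands. The diseases are named in words, the codes are in brackets, a questionnaire history is taken as well, and an electrocardiogram is recorded at baseline. A reader might infer that all prevalent disease is misclassified, or that the phase 1 associations are wrong by construction. The text does not support that. Misclassification follows only where status rests on the record check, and simple under-recording that is equal in both groups leaves the prevalence ratio unchanged.

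**I25 is not wholly wrong for a past infarction.** This also stands, because old infarction (I25.2) lies inside it. The fault is that the category is too broad and that I21-I22 are absent.

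**Phase 2 is untouched.** A reader might infer that missed strokes or stable angina would be counted as disease-free at entry and confuse new events with old ones. The article has no disease-free entry requirement and no previous-event flag for that purpose, and specialists confirm the follow-up events. Only a baseline disease covariate, if one is used, would carry the error into phase 2.

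**This is a condensed article, and a pilot is planned.** A fuller code list may exist. But the article does not leave the codes out; it prints a specific list that is faulty. The pilot is a good place to test the list, though testing would not by itself correct it.

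**Conclusion.** The point holds in limited form. Three printed code-and-disease pairs are faulty: I25 is over-broad and incomplete for infarction, I20.0 is too narrow for angina, and I64 is too narrow for stroke. Where case status rests on the record check, recorded angina and stroke will be too few, which lowers prevalence and precision. Infarction will both gain false cases and lose true ones, which can distort its association with PAD. The effect is confined to the phase 1 secondary objective and to any baseline cardiovascular-disease covariate. The prevalence of PAD and the composite follow-up outcome are outside its reach.

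The size cannot be derived from the documents. The 30% to 70% range for specifically coded strokes and the 8% versus 4% example are assumptions that show only the mechanism. The conclusion rests on the standard ICD-10 headings and on the record check having some influence on case status, which the article implies but does not spell out.

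**What to change.** Replace the code list in the baseline section and on the data form:

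- stroke: I60-I64, plus I69 for sequelae of stroke;
- angina: I20, all subcodes;
- myocardial infarction: I21-I22 and I25.2;
- the rest of I25: a separate item, chronic ischaemic heart disease;
- transient ischaemic attack G45 and PAD I73.9: as now.

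Add one sentence that says which source prevails when the questionnaire and the record disagree, so that all 24 centres classify alike.

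The cost is a small edit to the data form before the 120-case pilot, which can then check the revised list. The same record is reviewed, with no extra visit or test. The one addition is a separate item for chronic ischaemic heart disease.

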#### Follow up (cohort study)

After determination of the AAI the subject will enter in one of the cohorts (AAI>= 0.9: cohort without peripheral arterial disease; AAI < 0.9 cohort with peripheral arterial disease).

The successive controls will be undertaken every 6 months after the last visit, by telephone interview. The appearance of any of the events will be registered in the data collection protocol: transitory ischaemic accident, ictus, angina, myocardial infarction, symptomatic abdominal aneurysm and mortality attributable to vascular causes.

The main variable of response will be the appearance of cardiovascular events as a combined compound variable [27] made up of the following diseases:

#### Morbidity

-Coronary disease: 1) angina, 2) acute myocardial infarction

-Cerebrovascular disease: 1) transient ischaemic attack, 2) ictus

-Symptomatic aneurysm of the abdominal aorta

These events will be confirmed by a cardiologist, neurologist and vascular surgeon, respectively.

#### Mortality

-Ictus

-Myocardial infarction

-Sudden death attributable to cardiovascular events

-Aneurysm of the abdominal artery

-Complications of PAD.

The mortality will be studied by: control of the computerised clinical history, telephone interview with a relative and personal or telephone interview with general practitioner responsible for the patient. If adequate information is not obtained by the above sources, the emergency departments (SEM) and emergency paramedical services (061) and, if necessary, the statistical registries of deaths (Department of Health) will be consulted.

### Statistical analysis

#### Sample size

The sample size for the cohort study has been calculated with an alpha risk of 0.05, a beta risk of 0.20 in a bilateral contrast, taking a relationship of exposure (altered AAI) compared to no exposure (normal AAI) of 1:9 into account. To do this 301 subjects in the group of patients diagnosed with peripheral arterial disease (pathologic AAI) and 2709 patients in the group without peripheral arterial disease (normal AAI) are required to detect a minimum relative risk of the main variable of response of 2, accepting an incidence of the cardiovascular disease studied in the general population of 5.2% [24]. The rate of loss to follow up has been calculated to be of 10%.

This sample size also ensures correct estimation of the populational prevalence of asymptomatic AAI in our medium with a precision of 2%, accepting an alpha risk of 0.05 in the most unfavourable case of having to detect a prevalence of 50%.

#### Data analysis

This will be performed with the Stata 9 statistical package after the introduction of the data in a database (Acces).

Quantitative variables will be compared with the Student's t test and analysis of variance (ANOVA) will be performed, using the corresponding non parametric tests when necessary. Qualitative variables comparisons will be determined using the Chi squared test.

An analysis of survival of each vascular event will be performed according to the presence/absence of PAD with the Kaplan-Meier curves. Cox multivariate regression models will be used to compare the probability of having a cardiovascular event in the follow up cohorts, adjusting for the necessary covariables. The relative risk (hazards ratio) will be analysed with a confidence interval of 95%.

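### The only tests named that can serve the phase I association objective are unadjusted, so age and sex can mask or create associations with PAD

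*Protocol article*

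**What the plan says.** The Methods/Design section of the protocol article sets the phase I secondary aim, which ends with risk factors: "The secondary aim is to study the association of PAD, especially in the silient forms, with other previous or prevalent cardiovascular events and cardiovascular risk". The Background states the same objective.

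The Data analysis section then gives the methods. For continuous data: "Quantitative variables will be compared with the Student's t test and analysis of variance (ANOVA) will be performed", with non-parametric counterparts where needed. For categorical data: "Qualitative variables comparisons will be determined using the Chi squared test". The remaining methods are Kaplan-Meier curves for vascular events and one model with covariates: "Cox multivariate regression models will be used to compare the probability of having a cardiovascular event in the follow up cohorts, adjusting for the necessary".

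On the role of age and sex, the Background lists the modifiable risk factors and adds: "while age and sex are non modifiable factors". The Abstract sets the sample at 3,010 people over 50. No upper limit is given, and the Discussion explains how risk scores will be handled in those older than 74.

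On sampling, the Study Population section says: "A simple randomised sample will be undertaken until achieving the required sample size". The main phase I aim is to "determine the prevalence of symptomatic and asymptomatic PAD in a general population attended in primary care", and the Discussion presents the result as the real prevalence in the general population.

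**The concern.** A Cox model for incident events cannot answer a cross-sectional question. Of the methods named, that leaves only two-group tests without covariates for the phase I association objective. PAD prevalence can be expected to rise with age, and many risk factors change with age too, some upwards and some downwards. A crude comparison of people with and without PAD then mixes the factor's own association with the age difference between the groups. A factor commoner at younger ages, as smoking may be, would look weaker than it is. A factor commoner at older ages would look associated even if it were not. Sex can act in the same way.

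At stake is the reading of the whole phase I association table, including the results for silent PAD that the objective singles out. The prevalence estimate raises a related but smaller issue. If willingness to attend differs by age or sex, the age-sex mix of the 3,010 will differ from that of the registered population, and a crude percentage carries that difference.

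**Working it through.** **The plan's own figure.** The only stated number that bears on phase I is the prevalence precision of 2% at 50% prevalence (Sample size section). The half-width is 1.96 × √(p(1−p)/N).
- p = 0.5, N = 3,010: 1.79 points, so the stated 2% is met.
- p = 0.10 (implied by the 1:9 exposure ratio): 1.07 points.

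This figure covers sampling error only.

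**Which method serves which objective.**
- Phase I association: t test, ANOVA, non-parametric tests, chi-squared; no covariates.
- Phase II event risk: Kaplan-Meier, and Cox with covariates.

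The article gives no age-specific rates of PAD, risk factors or response. All inputs from here on are assumptions, chosen to show the mechanism.

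**Masking.** Two equal age strata; smoking 30% (younger) and 10% (older); within-stratum odds ratio 2.0. Take PAD in non-smokers as 3% and 12%. PAD in smokers is 2o/(1+2o), where o is the odds in non-smokers: 5.83% and 21.43%. Proportions of the whole sample:
- smokers with PAD: 0.5 × 0.30 × 0.0583 + 0.5 × 0.10 × 0.2143 = 0.01945
- smokers without PAD: 0.20 − 0.01945 = 0.18055
- non-smokers with PAD: 0.5 × 0.70 × 0.03 + 0.5 × 0.90 × 0.12 = 0.0645
- non-smokers without PAD: 0.80 − 0.0645 = 0.7355

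Crude odds ratio = (0.01945 × 0.7355)/(0.18055 × 0.0645) = 1.23.

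With PAD of 3 or 4% in the younger and 12 or 14% in the older stratum, in all four combinations:
- read as rates in non-smokers: crude odds ratio 1.16 to 1.35
- read as rates in the whole stratum: 1.11 to 1.28

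So a within-age 2.0 appears as about 1.1 to 1.35.

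**Creating an association.** Two equal age strata, no association within either. The rejection probability is for a two-sided 5% test with 301 people with PAD and 2,709 without.

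| PAD, younger/older | Factor, younger/older | Crude OR | Rejection probability |
|---|---|---|---|
| 5% / 15% | 45% / 55% | 1.12 | about 15% |
| 5% / 15% | 40% / 60% | 1.25 | about 45% |
| 4% / 20% | 35% / 65% | 1.58 | about 97% |

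**Prevalence under differential response.** Assumed PAD 4%, 10% and 20% at ages 50-64, 65-74 and 75+; population shares 50%, 27% and 23%.
- True prevalence: 0.50 × 0.04 + 0.27 × 0.10 + 0.23 × 0.20 = 9.3%.
- Response 70%, 65%, 40%: 0.04995/0.6175 = 8.1%, a shift of 1.2 points.
- Response 70%, 65%, 50%: 0.05455/0.6405 = 8.5%, a shift of 0.8 points.
- Response 70%, 65%, 60%: 0.05915/0.6635 = 8.9%, a shift of 0.4 points.

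The half-width at 9.3% is 1.04 points. With equal response in all age groups the shift is zero.

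**The case against.** The article condenses a fuller protocol, and the analysis plan is not shown. The Data analysis section does not tie the t and chi-squared tests to phase I by name, and it does not exclude a multivariable model. The authors know that age and sex matter, collect the covariates and adjust in phase II. Phase I is called descriptive, and a crude comparison is a legitimate descriptive step.

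Much of this stands. The quoted sentence is not wrong in itself, and an adjusted phase I model may exist elsewhere. But the section does more than stay silent: it lists methods for both phases and attaches adjustment to one. Followed as written, it gives no adjusted answer to a stated objective.

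The sampling side needs more restraint. A reader might infer that drawing until the target is reached biases prevalence. It does not: continued random draws are unbiased unless response is differential, and a fixed number of invitations would carry the same risk. No response rate is given, the 10% loss concerns follow-up, and the flow diagram, which may cover non-response, is not shown. The illustrated shifts stay below the stated 2% precision. A reader might also make something of the target being described once as those registered with the centres and once as those attended in primary care. In a translated text these can mean the same, and no consequence follows from the wording.

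**Conclusion.** The point holds for the association objective: as written, phase I is served only by unadjusted tests, and in a sample over 50 without an upper age limit these can mask or create associations. On the assumed rates the distortion is material: a within-age 2.0 shrinks to about 1.1 to 1.35, and a null association grows to about 1.1 to 1.6.

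Two stronger conclusions are not supported. One is that phase I associations will be confounded by a known amount, or reversed: the masking examples show attenuation only, and every input is assumed. The other is that non-response does shift the prevalence: it could, but neither size nor direction can be derived from the article. Standardised prevalence is therefore a worthwhile addition, not the correction of an error. No stated figure is shown to be wrong.

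**What to change.** 1. State in the Data analysis section that phase I associations will be estimated by logistic or prevalence-ratio regression, with age as a continuous term and sex in every model, reported with 95% confidence intervals. Keep the t, ANOVA, non-parametric and chi-squared tests as description. If the full protocol already holds such a model, one sentence in the article is enough. The cost is wording: age and sex are needed for the risk scores anyway.
2. As a secondary improvement, record age, sex and centre of everyone drawn, including those who do not attend. Report the response rate, and give prevalence standardised to the age-sex distribution of the registered over-50 population of the 24 centres beside the crude figure. The record should start with the first draw, because it may not be recoverable later. The cost is a log and a slightly wider interval. Standardisation does not remove response bias within age-sex strata, and the report should say so.
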